## Abstract

**Background:**

Type 2 diabetes mellitus (T2DM) is highly prevalent in the United States and represents a significant public health challenge. Telehealth interventions have shown promise for improving T2DM outcomes, but their effectiveness is often limited by disparities in digital literacy and access, especially in rural areas. To address this gap, we propose an innovative, individualized lifestyle modification intervention delivered via phone call to support glycemic control.

**Objective:**

This paper outlines the protocol for a pilot study designed to assess the feasibility and preliminary effectiveness of an artificial intelligence–assisted intervention for T2DM self-management in rural settings.

**Methods:**

The study uses the preparation phase of the MOST (Multiphase Optimization Strategy) framework to evaluate two components: (1) automated versus human health coaching and (2) fixed versus adapted gamified financial incentives, based on participants’ daily engagement with automated monitoring calls. We aim to enroll 88 adults with T2DM and hemoglobin A_1c_ (HbA_1c_) levels between 6.5% and 11.5%. Participants receive daily interactive voice response calls tracking diet, physical activity, medication adherence, and blood glucose, and weekly coaching based on randomization. In the fixed-reward arm, participants earn US $0.60 per day; in the adaptive arm, rewards start at US $0.20 and increase weekly, with penalties for missed days. Primary outcomes include feasibility metrics and preliminary changes in HbA_1c_. Semistructured interviews will assess patient experience.

**Results:**

This study was funded by the National Institute of Diabetes and Digestive and Kidney Diseases. As of October 2025, we have enrolled and completed data collection for 88 participants. We expect to complete the feasibility analysis by December 2025.

**Conclusions:**

This pilot and feasibility study evaluates a low-tech, artificial intelligence–assisted T2DM intervention designed to reduce digital barriers and inform a future MOST optimization trial.

**Trial Registration:**

ClinicalTrials.gov NCT05344859; https://clinicaltrials.gov/study/NCT05344859

**International Registered Report Identifier (IRRID):**

DERR1-10.2196/70271

## Introduction

Type 2 diabetes mellitus (T2DM) is a major public health crisis exerting a considerable burden on individual health and the health care system across the United States. Its prevalence is especially high in the Deep South of the United States and in rural areas compared to urban settings [1-3]. Glycemic control through a combination of diet, physical activity (PA), glucose monitoring, and medication adherence has been shown to be effective in T2DM management (reduced hemoglobin A_1c_ [HbA_1c_]) [4-8]. However, the majority of individuals with T2DM are unable to adhere to the diabetes management guidelines, and this problem is amplified in populations with low health literacy, higher poverty levels, or in remote rural settings [9-11].

T2DM significantly impacts clinical resource utilization because of its frequent comorbidity with cardiovascular and chronic kidney diseases [12-14]. Primary care providers serve as the initial point of contact for most patients with chronic conditions [15] and handle, on average, 4.6 problems per patient visit for patients with diabetes [14,16]. This significant workload and the shortage of primary care professionals lead to primary care access issues, highlighting the need to empower patients’ behavior modification outside of the clinic. Increasing patients’ knowledge and confidence to self-monitor and modify their health behavior is crucial to improving their health outcomes while conserving limited clinic resources.

Regular self-monitoring (tracking) helps informed decision-making [17-19]. For example, regular blood glucose monitoring provides objective feedback on glycemic control [20]. Similarly, tracking PA (steps) and dietary intake helps alter respective behaviors [21,22] and can influence medication adherence behaviors [23]. Therefore, self-monitoring (tracking) of behaviors has great potential to affect diabetes related health behaviors. However, maintaining diaries or apps for diabetes self-management activities has been shown to increase participant burden and reduce long-term engagement due to loss of interest, complexity, and digital literacy barriers [24,25]. While self-monitoring alone sees benefits, this intervention is often paired with health coaching to provide direct feedback on behaviors, plus provide goal setting and suggestions of dietary or PA alternatives where appropriate. Indeed, digital health coaching has been shown to be effective in improving T2DM outcomes, particularly lowering HbA_1c_. A systematic review and meta-analysis of 28 studies, 82% of which were randomized trials, found that high-intensity digital coaching interventions are more effective in managing T2DM when compared to usual care [26].

Despite self-monitoring and health coaching’s potential to aid in diabetes self-management, the effectiveness of their delivery is hindered by the digital divide [27]. The adoption of digital technologies like smartphones and tablets involved in such interventions is growing, but not uniformly, and sees disparities by age, gender, education, and income. For example, while 97% of adults aged 30-49 years have a smartphone, this rate drops to 91% for adults aged 50-64 years and to only 79% of adults aged 65 years and older [28,29]. Even when given access to a tablet or smart device, many adults are not sufficiently technically proficient to operate them or the software or apps loaded onto them [30]. To ensure broader accessibility and maintain digital equity, there is a need for a scalable, minimally digital intervention that can operate without a mobile app or high-speed internet connectivity. In response to this, the proposed study’s intervention leverages the most pervasive and simplest technology—a telephone call, with no expectations of internet availability or smart device-based application proficiency. Use of telephone calls ensures inclusiveness and minimizes barriers for those who may lack or be unable to use smartphones or texting features for either self-monitoring or health coaching.

A telephone call-based self-monitoring and health coaching intervention would be responsive to the need for tech-agnostic self-monitoring for T2DM, but it is human resource-heavy. Hence, we are proposing artificial intelligence (AI)–assisted daily monitoring and automated health coaching as a scalable and low-cost alternative using the interactive voice response (IVR) system. The goal is to use accessible technology to optimize the reach and effectiveness of health coaching. To date, no study has reported using telephone calls for AI-assisted daily monitoring and health coaching focused on the four essential behaviors for glycemic control—PA, diet, medication adherence, and blood glucose monitoring. The daily nature of these automated calls for behavior monitoring presents a challenge for adherence. Rewards, especially monetary rewards, have been shown to provide significant extrinsic motivation toward behavior changes [31-33]. Gamification is also increasingly recognized as an effective method to stimulate adherence [34,35]. Very few studies have compared adaptive gamified financial incentives with fixed financial rewards. We incorporate gamification by implementing a gamified rewards scheme [31] based on participants’ consistency of answering daily self-monitoring calls to improve self-monitoring (tracking) behavior. GODART’s (Gamified Optimized Diabetes Management with Artificial Intelligence-Powered Rural Telehealth) theoretical framework is based on the social cognitive theory (SCT) for behavior change.

The proposed study aims to pilot GODART’s core feature: an automated behavior monitoring program using natural language processing (NLP) and two intervention components. The first intervention component (technology optimization experiment) will assess the feasibility of automated coaching and human coaching, and estimate preliminary effects of automated coaching compared to human coaching. The second intervention component (resource optimization experiment) will assess the feasibility of fixed and adaptive gamified rewards and estimate the preliminary effects of adaptive rewards compared to gamified rewards. Overall, we will assess the feasibility of our GODART study protocol in terms of recruitment, retention, and adherence. We hypothesize that the proposed interventions will be feasible and acceptable, and show early promise for reducing HbA_1c_ in adults with T2DM.

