**Figure 1 figure1:**

Overview of the GODART intervention structure; all study participants receive the GODART core technology (ABMS), but are randomized to one of two optimization experimental conditions: the Technology Optimization Experimentation, comparing human versus automated health coaching, or the Resource Optimization Experimentation, comparing fixed versus adaptive gamified rewards. ABMS: automated behavior monitoring system; AI: artificial intelligence; GODART: Gamified Optimized Diabetes Management with Artificial Intelligence-Powered Rural Telehealth.

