### Study Design

The GODART study uses the MOST (Multiphase Optimization Strategy) design, grounded in resource management principles and continuous improvement [36-38]. This study aligns with the preparatory phase of MOST. We are applying factorial experimentation as part of this MOST preparatory phase to assess the feasibility of two different intervention components (experimentations), with two levels in each group, yielding four experimental conditions. The Technology Experimentation component (Figure 1) focuses on comparing automated coaching through IVR with traditional human-delivered coaching. The goal here is to assess the feasibility of optimizing health coaching by leveraging accessible technology and assessing the preliminary effect when compared to human coaching. The Resource Experimentation focuses on assessing the feasibility and preliminary effect of the adaptive (gamified) rewards when compared to the fixed rewards program. Upon completion of the intervention, all participants will be invited to complete an exit interview to gauge expectations and perceived benefits and to collect suggestions for protocol improvement. Study findings will help us assess the feasibility of the protocol, acceptability of the intervention components, and their preliminary effectiveness in reducing HbA_1c_, leading to a confirmatory optimization trial. Figure 2 shows a schematic diagram of the study flow.

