### Baseline Assessments

Once participant eligibility is confirmed from screening, the blood values used in the in-person screening visit described above are used as baseline values. In addition, a baseline survey packet consisting of sociodemographic questions and five validated survey instruments is sent electronically to the participants. The survey instruments are as follows: The Spoken Knowledge in Low Literacy in Diabetes Scale (SKILLD) assesses patients’ understanding of diabetes management [42]; the Patient Health Questionnaire-4 screens for symptoms of anxiety and depression [43]; The Diabetes Distress Scale measures the emotional burden associated with diabetes management [44]; The Diabetes Empowerment Scale evaluates patients’ self-efficacy in controlling diabetes [45], and the EQ-5D [46] survey assesses health-related quality of life. All study data are collected and securely stored in the REDCap database. If participants are unfamiliar or uncomfortable with completing the survey packet electronically or if they lack an email address, the survey packets are mailed to their preferred address. Included in the packet is a prepaid stamped envelope to return the survey packet. Upon receipt, survey responses are uploaded to REDCap, and the physical copies are stored in a secure cabinet at the research site.

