### Randomization

Computer-generated randomization assignment was done for all consented participants. We implemented a permuted block randomization with varying block sizes, blinded to the assessment team. Participants were randomized to four experimental conditions based on a 2 by 2 factorial design with equal probability allocation. The randomization list is concealed within the REDCap randomization module. We have programmed this such that the participant can be randomized and allocated only to an experimental condition after it is confirmed that baseline data have been collected and entered. Once the primary outcome measures are entered in REDCap, the study staff members can assign the participants to their respective experimental conditions. The statistician and the Principal Investigators are blinded, but the participants and the health coach are not blinded. All participants enrolled in the study were randomized to one of the four arms:

Arm 1: Adaptive reward+weekly automated coachingArm 2: Adaptive reward+weekly human coachingArm 3: Fixed reward+weekly automated coachingArm 4: Fixed reward+weekly human coaching

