#### Experimentation Group 1: Automated Versus Human Health Coaching

Participants receive weekly human health coaching or automated health coaching for 24 weeks. Participants randomized to human health coaching receive a call from a human health coach, while those randomized to automated health coaching receive a rules-based automated health coaching call delivered via IVR. Topics include meal timing and spacing, monitoring nutrients for glycemic control, benefits of regular exercise, medication adherence, and consistent blood glucose monitoring.

Both coaching methods rely on data from the prior week’s AI-assisted ABMS calls, which are populated into a coaching dashboard using Nutritionix and participant-reported data. In both coaching methods, the human health coach reviews participants’ intake and performance against weekly goals. However, the scope and delivery of feedback differ. In the automated health coaching method, participants receive feedback via an IVR system using a rule-based AI engine. The human health coach provides weekly dietary suggestions specifically related to carbohydrate and saturated fat intake. The system flags whether the intake in these categories is within range or elevated, and highlights contributing food items. Based on this information, the coach inputs tailored suggestions that are aligned with participants’ health goals, which are then delivered automatically via IVR. Feedback related to medication adherence, blood glucose monitoring, and PA is also delivered automatically via IVR, based on participant-reported data. In the human health coaching method, the same intake data are reviewed, but coaching occurs through direct human interaction, allowing for more nuanced discussion around dietary patterns, behavior change strategies, and personal barriers. The coach is able to engage participants in deeper conversation, explore the context behind food choices, and collaboratively problem-solve to support goal attainment.

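### The package-level HbA1c objective and hypothesis have no concurrent comparator, and the only available evidence, change from the eligibility HbA1c, is biased toward a fall

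*Protocol article*

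**What the plan says.** The abstract's Objective says the pilot will "assess the feasibility and preliminary effectiveness of an artificial intelligence–assisted intervention for T2DM self-management in rural settings". The Introduction closes with the hypothesis: "We hypothesize that the proposed interventions will be feasible and acceptable, and show early promise for reducing HbA_1c_ in adults with T2DM". The Study Design section ends by looking forward to the "acceptability of the intervention components, and their preliminary effectiveness in reducing HbA_1c_, leading to a confirmatory optimization trial".

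The same Introduction paragraph and the Study Design section also give comparative aims: the preliminary effect of automated against human coaching, and of adaptive against the other reward scheme.

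On allocation, the Randomization section says: "Participants were randomized to four experimental conditions based on a 2 by 2 factorial design with equal probability allocation". The four arms cross the two coaching modes with the two reward schemes. The Figure 1 caption says every participant receives the core monitoring system. The sections on delivery of materials and on orientation give everyone the pedometer, glucometer, education packet and orientation session. On coaching: "Participants receive weekly human health coaching or automated health coaching for 24 weeks". Both reward schemes pay.

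Eligibility requires an HbA1c of 6.5% to 11.5%. Under Baseline Assessments, "the blood values used in the in-person screening visit described above are used as baseline values".

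The analytic strategy models effects as component-by-time interactions. It calls a component or combination active on a mean HbA1c reduction of 0.5 points between baseline and month 6.

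**The concern.** The randomization can show which version of the program does better. It cannot show whether the program lowers HbA1c, because no participant goes without it. The abstract objective and the HbA1c half of the hypothesis are worded so that they need an answer to that second question, and only an uncontrolled before-after change can supply one.

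That change leans one way. Requiring at least 6.5% on one test and reusing the same test as baseline favors people whose value happened to be high that day. Secular trends and changes in usual care over six months are equally inseparable from an effect. A fall seen in all arms could therefore be read as early evidence for the package and carried into the optimization trial. The Strengths and Limitations section mentions neither the missing untreated comparator nor regression to the mean.

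**Working it through.** **1. What the plan's own power figure refers to.** The inputs under Sample Size Justification are 88 patients, 15% attrition, correlation 0.5 and d = 0.572. The evaluable number is 88 × 0.85 = 74.8, or 37.4 per level. The residual SD is √(1 − 0.5²) = 0.866 and the SE is 0.866 × √(2/37.4) = 0.200. Then 0.572/0.200 − 1.96 ≈ 0.90, which gives power of about 81.5% (80.4% with the noncentral t). The stated 80% is reproduced, and so are the companion effect sizes of 0.63 and 0.472. This power belongs to contrasts between component levels and says nothing about the package.

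**2. Expected fall with no effect.** From the plan: window 6.5 to 11.5, SD 1.5, correlations 0.3, 0.5 and 0.7. Assumed: source mean μ of 7.0 to 8.0% (not in the documents), a normal and stationary distribution, and 1.5 as the source SD.

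Mean of those selected: m = μ + 1.5 × [φ(a) − φ(b)] / [Φ(b) − Φ(a)], with a = (6.5 − μ)/1.5 and b = (11.5 − μ)/1.5. For μ = 7.0, a = −0.333 and b = 3.0, so m = 7.0 + 1.5 × (0.377 − 0.004)/0.629 = 7.89. For μ = 7.5 and 8.0, m = 8.12 and 8.39.

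Untreated fall = (1 − ρ)(m − μ), where ρ is the correlation in the source population.

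**3. Which correlation the plan means.** An ANCOVA correlation would normally describe enrolled patients. Selection narrows the baseline spread: the SD among those selected is 0.98, 1.06 and 1.13 for the three means. An enrolled-sample r therefore implies a larger ρ: ρ² = r² / [k²(1 − r²) + r²], with k = selected SD/1.5. For μ = 7.0 and r = 0.5, k² = 0.428 and ρ² = 0.25/(0.428 × 0.75 + 0.25) = 0.438. So ρ = 0.66, and the fall is 0.34 × 0.89 = 0.30.

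| Source mean | Fall if the plan's 0.3 / 0.5 / 0.7 are source-population values | Fall if they are enrolled-sample values |
|---|---|---|
| 7.0% | 0.62 / 0.44 / 0.27 | 0.50 / 0.30 / 0.15 |
| 7.5% | 0.43 / 0.31 / 0.19 | 0.37 / 0.23 / 0.12 |
| 8.0% | 0.27 / 0.19 / 0.12 | 0.24 / 0.15 / 0.08 |

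At a source-population correlation of 0.9, outside the plan's range, the fall is only 0.04 to 0.09 over these means. The Results section reports 162 people consenting to HbA1c screening and 88 randomized, but not why the others were lost, so it cannot narrow the range.

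**4. Before-after change against randomized contrast.** Trials of 88 patients were simulated with no effect, μ = 7.0 and source-population ρ = 0.5. The mean fall was 0.44, and a before-after test was significant in 84% of trials. The 44 versus 44 contrast in change averaged zero and rejected in 5%. At μ = 7.5 the before-after test was significant in 53% (ρ = 0.5) and 33% (ρ = 0.7). The plan does not schedule such a test. The simulation shows only how the two kinds of evidence behave.

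**The case against.** The strongest reply is that the right aims are already there. The Introduction and Study Design state the two component comparisons, the hypothesis follows them and speaks of interventions in the plural, and the Study Design sentence refers to components. The models use component-by-time interactions, in which regression to the mean cancels. Feasibility is primary in the Outcomes section, the study is described as preparatory and not definitive, and a factorial without an untreated cell is a legitimate way to choose between component levels. All of this stands, and it confines the point to the abstract objective, the HbA1c half of the hypothesis and the closing sentence of Study Design. It does not supply a reference for a reduction in HbA1c, which those sentences leave unnamed.

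On size, the reply is that the source mean is assumed, that the plan calls 0.5 conservative and 0.7 more realistic, and that its correlations most naturally describe enrolled patients. This also stands and lowers the figures, as the right-hand column shows.

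A reader might infer that the trial has no comparator at all, that its effect estimates are biased, or that the sponsor plans to report an all-arm fall as effectiveness. The documents support none of these. The component contrasts are randomized and concurrent, and no all-arm before-after test is planned. The one criterion worded as a before-after fall is the 0.5-point activity rule. Correcting that rule is a separate matter and would not rescue the package claim, because contrasts between levels are silent on it.

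**Conclusion.** The point holds for the package-level wording only. The missing comparator is a fact of the design and needs no assumption. The size of the bias does. With SD 1.5 and a source mean of 7.0% to 8.0%, the untreated fall is about 0.12 to 0.62 points if the plan's correlations are source-population values, and about 0.08 to 0.50 if they are enrolled-sample values. On the enrolled-sample reading it is 0.15 to 0.30 at r = 0.5 (30% to 60% of the plan's 0.5-point benchmark) and 0.08 to 0.15 at r = 0.7 (16% to 30%). Secular and usual-care changes come on top, in a direction the documents do not allow one to fix. Regression to the mean reaches 0.5 on its own only with a low source mean and a low correlation. Elsewhere it supplies part of an apparent benefit. The randomized component contrasts are unaffected.

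**What to change.** - **Abstract objective, HbA1c part of the Introduction's hypothesis, closing sentence of Study Design:** restate as estimating the preliminary effects on HbA1c of automated versus human coaching and of adaptive versus fixed rewards. While doing so, correct the Introduction's second aim, which contrasts adaptive with gamified rewards where Study Design contrasts adaptive with fixed.
- **Analytic strategy:** state that all-arm and within-arm change in HbA1c from baseline is descriptive, is uncontrolled, starts from the eligibility value, and will not be read as effectiveness of GODART.
- **Strengths and Limitations:** add the absence of an untreated comparator and regression to the mean from reuse of the screening HbA1c.

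An HbA1c from the medical record should not be offered as a substitute baseline. Candidates were found by querying clinical data, so that value may itself have been used for selection.

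No new arm, patient or procedure is needed. Data collection is complete, but the article describes the analysis as still pending, so the wording can be settled before results are interpreted. The price is a narrower effectiveness claim.
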